**Exclusion criteria for non-cancer arm participants:**

- Individuals with significant chronic diseases of other systems, such as severe cardiovascular diseases, uncontrolled diabetes, hypertension, and infectious diseases.
- Individuals who had abnormal results of tumor marker (CEA, CA19-9, CA125, PSA, AFP, etc.) examinations within the past year.

## **6 BASELINE CHARACTERISTICS**

The participants will be adults of 18-85 years with no prior cancer history. The cancer arm will include patients diagnosed with stage I/II gastric cancer. The non-cancer arm will consist of individuals with no known or suspected cancer diagnosis.

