| Number of Sites    | Single site                                                                                                                                                                                                                                                                                                                                                                                                                                                                                                                                                                                                                     |
| Rationale          | Gastric cancer remains as one of the leading causes of death worldwide. Detecting gastric cancer earlier is vital for managing the disease effectively, improvement of survival rates and reduction of morbidity. Blood-based liquid biopsy has emerged as a promising technology for the early detection of multiple types of cancer, which can complement traditional cancer screening methods in a non-invasive manner. We developed a novel liquid biopsy assay using multi-dimensional cell-free DNA (cfDNA) features from whole genomic sequencing (WGS) data for the detection of gastric cancer at early stages.        |
| Study Design       | A single-center prospective observational study will be used to develop and valid the gastric cancer early detection study. The study is divided into two phases. The first phase of the study will enroll ~250 participants, including ~100 stage I-II gastric cancer patients and ~150 non-cancer individuals, over a period of 8 months. The cfDNA profiles of these participants will be used to develop a multi-layer machine learning model for identifying cancer presences. The second phase of the study will enroll ~125 participants over a period of 4 months to validate the performance of the cfDNA-based assay. |

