|--------------------|------------------------------------------------------------------------------------------------------------------------------------------------------------------------------------------------------------------------------------------------------------------------------------------------------------------------------------------------------------------------------------------------------------------------------------------------------------------------------------------------------------------------------------------------------------------------------------------------------------------------------------------------------------------------------------------------------------------------------------------------------------------------------------------------------------------------------------------------------------------------------------------------------------------------------------------------------------------------------------------|
|                    | Second phase: ~50 stage I-II gastric cancer patients, ~75 non-cancer individuals.                                                                                                                                                                                                                                                                                                                                                                                                                                                                                                                                                                                                                                                                                                                                                                                                                                                                                                        |

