| Sample Enrollment    | The study will enroll participants who voluntarily register in this clinical study at Zhejiang Cancer Hospital. All participants will be pre-screened as per Inclusion and Exclusion Criteria.                                                                                                                                                                                                             |
| Test                 | Blood samples will be collected and processed at Zhejiang Cancer Hospital.                                                                                                                                                                                                                                                                                                                                 |
| Statistical Analysis | The comparison of continuous numeric data will be conducted using the Wilcoxon test. The comparison of proportions between groups will be conducted using the Fisher's exact test. The trend of continuous numeric data across ordered groups will be assessed using Jonckheere trend test. A two-sided P value of less than 0.05 will be considered significant for all tests unless otherwise indicated. |
| Overall Duration     | Estimated about 12 months                                                                                                                                                                                                                                                                                                                                                                                  |

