### 5 POPULATION

#### 5.1 Inclusion Criteria

Inclusion criteria for all the participants:

- 18 – 85 years old.
- Individuals without a prior history of cancer.
- Individuals with a plasma sample that was collected before initial screening tests and passed quality control (QC).
- Individuals who provided informed consent.

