**Inclusion criteria for cancer arm participants:**

- Individuals who were pathologically confirmed with gastric adenocarcinomas by biopsies without concomitant malignancies and received curative surgeries for gastric cancer.

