**Inclusion criteria for non-cancer arm participants:**

- Individuals who showed no signs of cancers based on routine physical examinations, including blood tests, ultrasound and CT, and no sign of gastric cancer from gastric cancer-specific screening tests.

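### Recruitment does not secure age or sex comparability between the arms, so the crude AUROC may be partly inflated and Phase 2 would not reveal it

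*Protocol*

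**What the plan says.** Age enters the protocol only as an eligibility window. Section 5.1 lists "18 – 85 years old" for all participants, and section 6 repeats the window: "The participants will be adults of 18-85 years with no prior cancer history". Sex is not mentioned as a design factor.

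The arms have their own entry criteria. Cases are "Individuals who were pathologically confirmed with gastric adenocarcinomas by biopsies without concomitant malignancies and received curative surgeries for gastric cancer". Controls are "Individuals who showed no signs of cancers based on routine physical examinations, including blood tests, ultrasound and CT", and must also be clear on tests specific to gastric cancer. Section 5.2 then removes from the non-cancer arm only "Individuals with significant chronic diseases of other systems, such as severe cardiovascular diseases, uncontrolled diabetes, hypertension, and infectious diseases", together with anyone who had an abnormal tumour marker in the past year. The only arm-specific exclusion for cases is stage III/IV disease.

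Arm sizes are preset by disease status. The synopsis says "The first phase of the study will enroll ~250 participants, including ~100 stage I-II gastric cancer patients and ~150 non-cancer individuals", and then "Second phase: ~50 stage I-II gastric cancer patients, ~75 non-cancer individuals". The primary outcome in both phases is the AUROC between these arms (synopsis; section 2.1). Section 8 names one source hospital and draws no distinction between phases.

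**The concern.** An AUROC between two arms measures everything that separates them, as far as the score can pick it up. The model is trained on genome-wide cfDNA features (fragment size, copy number, nucleosome coverage, substitutions; section 1.1). If some of these vary with age or sex, and the arms differ in age or sex, training will reward that component as if it were cancer signal.

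Neither safeguard in the protocol would expose this. Every fold of the five-fold cross-validation shares the imbalance of the Phase 1 sample. Phase 2 tests the locked assay in new people, but under the same criteria, at the same site and in the same case-to-control ratio, so an imbalance produced by recruitment is likely to recur. The sensitivity and specificity at the Phase 1 threshold would be affected in the same way.

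The control-only exclusions make comparability less safe to assume. If the excluded conditions become more common with age, which is plausible but not quantified in the protocol, they would remove older controls and leave older cases in place.

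**Working it through.** **The plan's own figures.** The protocol states no target AUROC, power or sample-size derivation, so there is no performance figure to reproduce. Its counts are consistent: 100 + 150 = 250 and 50 + 75 = 125, a ratio of 1:1.5 in both phases.

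**Inputs from the protocol.** Age window 18-85 for both arms; 50 cases and 75 controls in Phase 2; crude AUROC as the primary outcome.

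**Inputs assumed, because the protocol gives none.** Age SD of 11 years; mean age gap between arms of 0, 5, 10 or 15 years; within-arm correlation r between score and age of 0, 0.3 or 0.5; an AUROC of 0.80 in arms of equal age; normally distributed scores with equal variance in both arms.

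**Formula.** On a score with within-arm SD 1, an AUROC of 0.80 corresponds to a mean difference d = √2 × Φ⁻¹(0.80) = 1.414 × 0.842 = 1.190. An age gap adds r × gap / 11 to that difference. The observed AUROC is then Φ((d + r × gap / 11) / √2).

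**Worked case, r = 0.3 and gap = 10.** The added shift is 0.3 × 10 / 11 = 0.273. The total is 1.190 + 0.273 = 1.463. Dividing by 1.414 gives 1.034, and Φ(1.034) = 0.850.

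| Age gap (years) | r = 0 | r = 0.3 | r = 0.5 |
|---|---|---|---|
| 0 | 0.800 | 0.800 | 0.800 |
| 5 | 0.800 | 0.826 | 0.842 |
| 10 | 0.800 | 0.850 | 0.878 |
| 15 | 0.800 | 0.871 | 0.907 |

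The inflation is nil if either the gap or the correlation is zero. At r = 0.3 it runs from 0.03 to 0.07. The table takes the case where the score and the age gap point the same way, which is the direction that training on imbalanced arms rewards. If the Phase 2 gap ran opposite to Phase 1's, the shift would be downward.

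**After matching.** With the gap at 0 and the same sex mix in both arms, age or sex alone has an AUROC of 0.50. At 50 versus 75 the Hanley-McNeil 95% interval around 0.50 is 0.40 to 0.60.

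**The case against.** The strongest reply is that the protocol does not show that any imbalance will arise. It gives no age or sex distribution. Several provisions apply to everybody: voluntary registration ("The study will enroll participants who voluntarily register in this clinical study"), one source hospital, plasma taken before the initial screening tests, and categorisation into arms after enrolment (subsection 7.3). These fit a single intake sorted by result at least as well as two separate recruitment streams. All of this stands. A reader might infer that controls come from a separate stream of healthy check-up volunteers and will be younger, but the documents support neither step. The chronic-disease exclusion is also narrower than it may look: it concerns significant disease, and it is unclear whether the qualifier on diabetes extends to hypertension. On either reading it applies to controls only.

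A second tempting inference is that the AUROC would measure age instead of cancer. Age alone can separate arms well: with assumed SDs of 10 and 12 years, a 10-year gap gives Φ(10 / √(10² + 12²)) = 0.74. But age is not among the feature families named in section 1.1. It can act only through cfDNA features related to it, so 0.74 is a benchmark and not a forecast of the assay's bias. Nor can one say that Phase 2 would confirm an artefact. That requires both an imbalance and a score that tracks it.

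Third, the shifts of 0.03 to 0.07 are smaller than the 95% half-width of about 0.08 for an AUROC of 0.80 with 50 versus 75. That gives the scale, but bias does not shrink with sample size and the interval does not allow for it.

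Finally, covariate adjustment is commonly left to the SAP, which is not at hand, so its absence from section 10 is no fault. Who enters each arm, however, is fixed by the protocol. An SAP can adjust where the arms overlap in age; it cannot create overlap that recruitment did not secure.

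**Conclusion.** The concern holds as a weakness of recruitment design. The protocol combines a 67-year age window (85 − 18), preset arm sizes and control-only health exclusions with no provision for age or sex balance, and Phase 2 repeats the arrangement. A shared imbalance would pass through cross-validation and validation into the primary outcome undetected.

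The claim is conditional: some inflation occurs if the arms differ in age or sex and the score partly tracks the difference. Direction and size cannot be determined from the documents, and every magnitude above rests on assumed inputs. Nothing in the protocol is miscalculated or contradictory on this point. It merits a change because the remedy is cheap and protects the interpretation of the primary result.

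**What to change.** **Recruitment, both phases.** Frequency-match the non-cancer arm to the cancer arm by 10-year age band and sex, filling quotas as cases accrue. The totals stay at about 150 and 75 controls. Because participants are categorised after enrolment, state the step at which the quota is applied.

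**Data.** Record sex explicitly. Age is implied by the eligibility check, but the protocol does not say that sex is collected. Report both by arm.

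**Phase 2 analysis (protocol or SAP).** Beside the crude AUROC, report an age- and sex-adjusted AUROC and the AUROC of a model with age and sex only. If the quotas work, that benchmark should lie near 0.50 and so checks the matching. If they fall short, it shows how much separation age and sex alone provide.

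**Cost.** Control accrual will be slower in the older bands, where the chronic-disease exclusion may bite hardest, and the 8- and 4-month windows may come under pressure. The reported AUROC may be less favourable. The added analyses need almost no extra work once sex is recorded. Matching on age and sex does not remove other differences that the control-only exclusions create.

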## **7 TREATMENT**

Not applicable

## **8 ENROLLMENT**

### **7.1 Participant recruitment:**

Participants will be sourced from Zhejiang Cancer Hospital.

### **7.2 Preliminary assessment and blood sample collection:**

After expressing interest or being approached for the study, participants will undergo a thorough assessment based on a predefined set of Inclusion and Exclusion criteria. This assessment ensures that only those individuals who meet the study's specific requirements and standards will be enrolled. A blood sample from each eligible participant will be collected following standard procedures.

### **7.3 Categorization:**

After enrollment, participants will be categorized into two main arms based on their medical status:

Cancer arm: participants diagnosed with gastric cancer.

Non-cancer arm: participants with no known or suspected cancer diagnosis.

### **7.4 Sample processing:**

Plasma will be isolated from blood samples within 4 hours of collection and then stored at 4°C.

cfDNA will be extracted from plasma within 72 hours and stored at -80°C for later whole-genome sequencing (WGS). cfDNA profiles will be generated from WGS data using in-house analyzing pipelines.

## **9 ADVERSE EFFECT REPORTING**

The in-vitro assay is in the same form as regular blood tests during physical examinations.

Participant will not be informed of the analysis results. We expect no additional adverse effects specifically associated with this liquid biopsy assay. Routine adverse effects reporting procedures will apply.

## **10 STATISTICAL ANALYSIS**

The comparison of continuous numeric data will be conducted using the Wilcoxon test. The comparison of proportions between groups will be conducted using the Fisher's exact test. The trend of continuous numeric data across ordered groups will be assessed using Jonckheere trend test. A two-sided P value of less than 0.05 will be considered significant for all tests unless otherwise indicated.

## **11. ETHICS AND REGULATORY REQUIREMENTS**

Written consent will be obtained from the participants from whom the samples are collected before the time of sample collection. The test requisition forms, records, and results will be kept in a confidential state and not be disclosed to any participants or third-party organizations/ individuals. All testing results will be only used for this research study. No testing result will be used for diagnostic or prescriptive purposes. All conducted procedures will be in compliance with the Declaration of Helsinki.

